## Abstract

**Background:**

Flash visual evoked potentials (FVEPs) are a reliable method for protecting visual function during spine surgery in prone position. However, the popularization and application of FVEPs remain limited due to the unclear influence of various anesthetics on FVEPs. Exploring the effects of anesthetic drugs on FVEP and establishing appropriate anesthesia maintenance methods are particularly important for promoting and applying FVEP. According to the conventional concept, inhaled narcotic drugs significantly affect the success of FVEP monitoring, FVEP extraction, and interpretation. Nonetheless, our previous study demonstrated that sevoflurane-propofol balanced anesthesia was a practicable regimen for FVEPs. Desflurane is widely used in general anesthesia for its rapid recovery properties. As the effect of desflurane on FVEP remains unclear, this trial will investigate the effect of different inhaled concentrations of desflurane anesthesia on amplitude of FVEPs during spine surgery, aiming to identify more feasible anesthesia schemes for the clinical application of FVEP.

**Methods/ design:**

A total of 70 patients undergoing elective spinal surgery will be enrolled in this prospective, randomized controlled, open-label, patient-assessor-blinded, superiority trial and randomly assigned to the low inhaled concentration of desflurane group (LD group) maintained with desflurane-propofolremifentanil-balanced anesthesia or high inhaled concentration of desflurane group (HD group) maintained with desflurane-remifentanil anesthesia maintenance group at a ratio of 1:1. All patients will be monitored for intraoperative FVEPs, and the baseline will be measured half an hour after induction under total intravenous anesthesia (TIVA). After that, patients will receive 0.5 minimum alveolar concentration (MAC) of desflurane combined with propofol and remifentanil for anesthesia maintenance in the LD group, while 0.7–1.0 MAC of desflurane and remifentanil will be maintained in the HD group. The primary outcome is the N75-P100 amplitude 1 h after the induction of anesthesia. We intend to use the dual measure evaluation, dual data entry, and statistical analysis by double trained assessors to ensure the reliability and accuracy of the results.

**Discussion:**

This randomized controlled trial aims to explore the superiority effect of low inhaled concentration of desflurane combined with propofolremifentanil-balanced anesthesia versus high inhaled concentration of desflurane combined with remifentanil anesthesia on amplitude of FVEPs. The study is meant to be published in a peer-reviewed journal and might guide the anesthetic regimen for FVEPs. The conclusion is expected to provide high-quality evidence for the effect of desflurane on FVEPs and aim to explore more feasible anesthesia schemes for the clinical application of FVEPs and visual function protection.

**Trial registration:**

This study was registered on clinicaltrials.gov on July 15, 2022. ClinicalTrials.gov Identifier: NCT05465330.

**Supplementary Information:**

The online version contains supplementary material available at 10.1186/s13063-024-08211-9.

## Strengths and limitations of this study

This prospective, randomized, controlled, open-label, patient-assessor-blinded trial aims to investigate the superiority effect of low inhaled concentration of desflurane combined with propofolremifentanil-balanced anesthesia versus high inhaled concentration of desflurane combined with remifentanil anesthesia on amplitude of FVEPs during spine surgery.This study will target a pragmatic endpoint, and the conclusion is expected to provide high-quality evidence for the effect of desflurane on FVEPs, aiming to explore more feasible anesthesia schemes for the clinical application of FVEPs and visual function protection. Notably, we intend to use the dual measure evaluation, dual data entry, and statistical analysis by double trained assessors to ensure the reliability and accuracy of the results.This study focuses on the effect of desflurane on FVEPs, and further studies could evaluate other inhalations or new anesthetics.

## Background

Loss of vision during prone surgery is a devastating complication that occurs due to a variety of reasons [1]. Intraoperative prone position can cause mechanical damage or ischemia of visual structures, causing postoperative visual loss or visual field defects [2]. The flash stimulus is transmitted from the retina to the optic nerve, optic chiasm, optic tract, lateral geniculate body, optic radiation, and visual cortex and converted from a light signal to electrical conduction. The evoked potential waveforms and data extracted from the occipital lobe area during surgery are called FVEPs. They reflect the integrity of the visual pathway in real time to guide intraoperative decision-making and prevent visual impairment or deterioration of the same caused by visual pathway damage [3–5]. Previous studies have shown that the amplitude is the main measure for evaluating FVEP, in addition to the latency value. Recently, a study showed that setting the early warning value as the FVEPs’ amplitude decreased by 20% from the baseline can detect new quadrant blindness [6]. FVEPs have become a reliable method for intraoperative protection of visual function in procedures jeopardizing visual pathway integrity or visual function, such as spine surgery in the prone position, neurosurgery of the sellar region, and similar.

Anesthetic drugs dramatically affect the amplitude and latency of FVEP and can even lead to the failure of FVEP extraction and interpretation, which limits the popularization and application of FVEPs. Exploring the effects of anesthetic drugs on FVEP and establishing appropriate anesthesia maintenance methods is particularly important for promoting and applying FVEP to promote perioperative visual function protection. Previously, it was commonly believed that neuromonitoring should be performed under total intravenous anesthesia and that inhalation anesthetics could significantly prolong the latency and reduce the amplitudes of evoked potentials, not confined solely to FVEPs but also extending to somatosensory evoked potential (SSEP) and motor-evoked potential (MEP) [7–10]. In their study, Reinacher et al. found that as the concentration of sevoflurane increased incrementally below 0.5 MAC, 0.75 MAC, and 1 MAC, the amplitude of MEP decreased in a concentration-dependent manner [11]. Similarly, Boisseau obtained consistent results in the intraoperative impact of sevoflurane on SSEP [12]. Vaugha et al. observed that sevoflurane and desflurane exhibited an increasing inhibitory effect on SSEP with increasing concentrations, reaching maximum inhibition at end-tidal concentrations of 3.2 and 4.9%, respectively [13]. Accordingly, TIVA was preferred for maintenance. However, some studies showed that the P100 amplitude was significantly reduced at plasma concentrations of 3.0 μg/ml propofol compared to 1.5 μg/ml, even during TIVA [14]. Besides, TIVA may not be suitable for lengthy surgeries needing motor-evoked potential monitoring with strict restriction for muscle relaxant supplements, especially during long-term spine surgery or neurosurgery.

Appropriate use of inhalation anesthetics, such as intravenous-inhalation balanced anesthesia, can significantly reduce the dosage of each type of anesthetic and may reduce the adverse effects of high-dose inhalation anesthetics or intravenous narcotics on electrophysiological monitoring [15]. Specifically, propofol acts mainly by activating gamma-aminobutyric acid receptors (GABA). In contrast, inhalation anesthetics act on N-methyl-D-aspartic acid receptors (NMDA) before and after synapses through various pathways, glycine, kainate, serotonin receptors, and potassium channels in addition to GABA, nicotinic choline, and calcium channels, which have a certain synergy between them. However, in 2017, Uribe et al. proposed that compared with TIVA, intravenous-inhalation balanced anesthesia based on desflurane significantly reduced the amplitude of FVEPs and prolonged their latency [16]. Conversely, our recent study showed that the effect of sevoflurane 0.5 MAC combined with propofol and remifentanil-balanced anesthesia on P100-N145 amplitude was not inferior to propofol-based TIVA. It suggests that sevoflurane-propofol balanced anesthesia is suitable as an optional anesthesia regimen for FVEPs [17]; however, the effect of inhalation at different concentrations on FVEPs remains controversial [16–18].

Desflurane is widely used in general anesthesia for its rapid recovery properties and unique advantages [19], including a low blood-gas partition coefficient, faster recovery of postoperative swallowing function and airway protective reflex, and high quality of recovery, conducive to the early recovery of respiratory function and orientation, in addition to early neurological evaluation. Furthermore, desflurane can significantly increase and prolong the muscle relaxant effect of nondepolarizing muscle relaxants compared with intravenous anesthesia [20]. For patients who need motor-evoked potential monitoring simultaneously, it can reduce the intraoperative muscle relaxant dosage and the incidence of intraoperative body movement and choking [21, 22], contributing to its wide use in general anesthesia during spine surgery. Until April 2024, 10 RCTs exploring the effects of anesthetics on FVEPs have been published, and only one of them involved desflurane, while high-concentration desflurane was not involved. A review of the Cochrane Library conducted in 2011, attempting to assess the impact of anesthetic drugs on intraoperative evoked potential, detected no randomized controlled trials (RCTs) [23]. There are only a few studies on the effects of desflurane on FVEPs under current monitoring conditions and the effect of different inhalation concentrations of desflurane on FVEPs.

Therefore, we aim to conduct a randomized controlled trial to compare the effects of low inhaled concentration of desflurane combined with propofol-remifentanil-balanced anesthesia versus high inhaled concentration of desflurane combined with remifentanil anesthesia maintenance on the amplitude and latency of intraoperative FVEPs monitoring. We hypothesize that a low inhaled concentration of desflurane combined with propofol-remifentanil-balanced anesthesia would be more suitable for monitoring FVEPs during spinal surgery.

## Methods

This protocol was prepared and presented following the Standard Protocol Items, and the enrolment, intervention, and assessment schedules are summarized in Fig. 1.

**Fig. 1 Fig1:**
[figure not shown]
Schedule of enrollment, intervention, and assessment. Asterisk symbol (*) indicates primary outcome; LD, low inhaled concentration of desflurane combined with propofol-remifentanil-balanced anaesthesia; HD, high inhaled concentration of desflurane combined with remifentanil anaesthesia; FVEPs, flash visual evoked potentials; PACU, post-anaesthesia care unit

### Study design and setting

In this prospective, randomized, controlled, open-label, patient-assessor-blinded and superiority trial, patients will be screened and recruited consecutively at Beijing Tiantan Hospital, Capital Medical University.

### Ethics and dissemination

The Ethical Committee of Beijing Tiantan Hospital, Capital Medical University approved the study on July 11, 2022 (KY2022-056–02). The study was registered on clincaltrials.gov on July 15, 2022 (NCT05465330). The first patient was recruited for the study on July 20, 2022; the estimated study completion date is June 1, 2024. In addition, it complies with the principles of the Helsinki Declaration, and the protocol (V1.0; April 8, 2022) is written in accordance with the SPIRIT 2013 guidelines (Supplementary Material 1).

The Good Clinical Practice (GCP) office of our hospital will perform an audit every 12 months, and the process will be independent from investigators and the sponsor. The Data Monitoring team in our research group is responsible for managing the day-to-day conduct of the trial and data management. Plans for communicating significant protocol modifications (e.g., changes to eligibility criteria, outcomes, analyses) to relevant parties (e.g., investigators, trial participants, trial registries, journals, regulators) will be submitted to the Ethics Committee and WHO Trial Registration system in time for approval before any subsequent studies are carried out. The study findings are meant to be published in peer-reviewed journals and presented at national or international conferences.

### Participants

The designated anesthesiologist in our team will participate in the recruitment of patients scheduled for elective spine surgery under general anesthesia in this trial. Inclusion criteria are as follows: (1) patients aged 18–65 years old; (2) American Society of Anaesthesiologists (ASA) status I-III grade; (3) willingness to sign written informed consent. Exclusion criteria are the following: (1) preoperative visual impairment; (2) severe liver and kidney disease; (3) history of asthma, uncontrolled chronic disease, such as high blood pressure, diabetes, unstable angina, or mental illness; (4) body mass index (BMI) ≥ 30 kg/m^2^; (5) abuse of analgesics and history of drug abuse; (6) allergy to silicone or rejection of visual evoked potential monitoring before surgery.

### Randomization and blinding

The patients undergoing elective spinal surgery will be randomly assigned to the LD or HD groups (Fig. 2). Eligible subjects or their legal representatives will be required to sign the written informed consent prior to randomization and surgery by the trained assessor of our team (for the flow chart, see Fig. 2). Supplemental file 1 introduces the details of the patient’s informed consent.

**Fig. 2 Fig2:**
[figure not shown]
Flow diagram: the schedule of enrollment, interventions, and assessments. LD, low inhaled concentration of desflurane combined with propofol-remifentanil-balanced anesthesia; HD, high inhaled concentration of desflurane combined with remifentanil anesthesia

Randomization will occur on the date of spine surgery. Block randomization will be conducted to allocate patients to the LD group or HD group at a 1:1 ratio. The randomized digital table will be generated by an independent researcher using SPSS 25 and will be placed in a closed, opaque envelope. A designated person not involved in anesthesia management or follow-up will perform the assignment randomization sequence to ensure blinding. After the patient enters the operating room, the attending anaesthesiologist will open the sealed envelope to obtain the assignment information.

The neuroelectrophysiologists (primary outcome assessors), neurosurgeons, follow-up assessors, and biostatisticians will be blinded to the grouping; however, the anaesthesiologists will be aware of the specific assignments, as the interventions in this trial require different anesthesia protocols. A designated experienced neuroelectrophysiologist will monitor intraoperative FVEPs for all patients.

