### Anaesthesia regimen

No pre-induction drugs will be administered to avoid latent interference effects with FVEPs. Baseline parameters will be monitored perioperatively, including blood pressure, electrocardiogram (ECG), pulse oxygen saturation, bispectral index (BIS), and body temperature. Anesthesia induction and maintenance of propofol will be conducted with a target-controlled infusion (TCI) device (Marsh model, Master TCI-Diprifusor, Fresenius, Brezins, France). After 5 min of preoxygenation, general anesthesia induction will be performed by sequence TCI propofol 5 μg/ml, bolus of remifentanil 1–2 μg/kg, and rocuronium 0.6 mg/kg intravenously to complete tracheal intubation. Respiratory parameters will be adjusted to a tidal volume of 8 ml/kg and a respiratory rate of 10–12 breaths/min; PaCO_2_ will be maintained at 35–45 mmHg. After induction of anesthesia, all patients will be maintained with TIVA (propofol 3–4 μg/ml plasma concentration and remifentanil 0.05–0.2 μg/kg/min) for 30 min to obtain baseline FVEP values. Next, for the patients in the HD group, we will administer desflurane (0.7–1.0 MAC of end-tidal concentration) and remifentanil (0.05–0.2 μg/kg/min) for maintenance, while desflurane (0.5 MAC) will be combined with propofol (1.5–2.5 μg/mL) and remifentanil (0.05–0.2 μg/kg/min) in the LD group. The plasma concentration of propofol will be adjusted in the LD group, and the MAC of desflurane will be titrated between 0.7 and 1.0 to maintain the BIS (BIS Vista monitor, Aspect Medical Systems, Natick, MA) between 40 and 50, primarily focusing and avoiding burst suppression. The mean arterial pressure (MAP) and heart rate (HR) will be maintained at ± 10% compared with baseline. The anesthesiologist will give vasoactive drugs such as urapidil, dopamine, esmolol, and atropine if the blood pressure and heart rate fluctuate >  ± 10%. Intraoperative body temperature will be maintained between 36 and 37°C.

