### Intervention

An ophthalmologist will examine all patients to ensure normal visual function one day before the surgery. The patients will also undergo intraoperative neurophysiological monitoring using electrodes placed subcutaneously or in a corkscrew, including FVEPs and electroretinography (ERG) monitoring (to ascertain efficient delivery of retinal light stimulation).

The corkscrew electrodes for FVEPs will be located in the occipital zero (OZ) (4 cm above the occipital trochanter), O1 (4 cm left lateral to the OZ), O2 (4 cm right lateral to the OZ), frontal zero (FZ) (midfrontal area, 10–12 cm above the nose), and 2 ground electrodes. Electrodes for ERG will be placed 2 cm from the lateral canthus of the patient’s eyes (Fig. 3). FVEP stimulation, data recording, and storage will be performed using the Medtronic NimEclipse neuromonitoring system, which provides goggles with 6 embedded light-emitting diode (LED) bulbs. The specific parameters will be as follows: white light source high-intensity LED, 1.1 Hz stimulation frequency, 5000 to 10,000 lx laser emission, smoothing bandpass 20 to 100 Hz, and 1 to 100 Hz filter bandpass [21–23]. Each pulse stimulation will last 10 ms. The same experienced neuroelectrophysiologist will monitor intraoperative FVEPs for all procedures. We named the vertical distance between N75 and P100 the N75-P100 amplitude and the vertical distance between P100 and N145 the P100-N145 amplitude and defined P100 as the latency of FVEPs in our study. We will measure the baseline amplitude and latency of FVEPs 30 min after anesthesia induction under TIVA in both groups, which will be marked as N75-P100 (TIVA), P100-N145 (TIVA), and P100 (TIVA). Then, anesthesia maintenance with the HD group or LD group will be implemented according to the randomization results. We will measure the amplitude and latency of FVEPs 60 min after anesthesia induction in LD or HD group, which will be accordingly marked as N75-P100 (LD), P100-N145 (LD), and P100 (LD) vs N75-P100 (HD), P100-N145 (HD), and P100 (HD). At each chosen time point, we will measure the N75-P100 amplitude, P100-N145 amplitude, and P100 latency 3 times and record the average of the measurements.

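### Nothing stops the unblinded anaesthesiologist from opening the allocation envelope before the common TIVA baseline is recorded, which exposes three baseline-relative secondary endpoints

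*Protocol article*

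**What the plan says.** All references are to the protocol article.

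- **Timing of allocation (Randomization and blinding, text after Fig. 2).** "Randomization will occur on the date of spine surgery", and "After the patient enters the operating room, the attending anaesthesiologist will open the sealed envelope to obtain the assignment information". This sets an earliest moment for opening. It is not tied to induction or to the baseline recording.
- **Who knows the arm (same section).** "The neuroelectrophysiologists (primary outcome assessors), neurosurgeons, follow-up assessors, and biostatisticians will be blinded to the grouping"; by contrast, "the anaesthesiologists will be aware of the specific assignments, as the interventions in this trial require different anesthesia protocols".
- **Common phase (Anaesthesia regimen).** Every patient has the same induction and is then kept on TIVA "for 30 min to obtain baseline FVEP values", with propofol allowed between 3 and 4 μg/ml and remifentanil between 0.05 and 0.2 μg/kg/min.
- **Where the arms part (Intervention).** "We will measure the baseline amplitude and latency of FVEPs 30 min after anesthesia induction under TIVA in both groups". After that: "Then, anesthesia maintenance with the HD group or LD group will be implemented according to the randomization results".
- **Use of the baseline (Study endpoints).** It is the denominator of the N75-P100 decline rate, the P100-N145 decline rate and the P100 latency prolongation rate, all secondary. The primary endpoint is the N75-P100 amplitude at 60 minutes, with no reference to baseline.
- **Failed recordings.** Remedy keeps such patients in the study. Statistical analysis counts subjects without available FVEP data as failures of their regimen and removes them from every analysis.

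**The concern.** A baseline is useful in a randomised comparison because it cannot depend on the arm. That is guaranteed if it is recorded before anyone who can influence it knows the allocation. Here the allocation is not needed until the baseline has been recorded, yet the person running the anaesthetic may learn it earlier and has room to choose drug levels within ranges while the baseline is being produced. If those choices differed by arm, even unconsciously, the denominators of three secondary endpoints would differ by arm too, and an apparent difference in decline or prolongation could come partly from the baseline.

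A second, smaller consequence is that a patient whose baseline cannot be recorded has by then been randomised without having received either study regimen. Dropping that patient is a post-randomisation exclusion for a reason unrelated to treatment.

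**Working it through.** **1. Sequence, from the text.** Operating-room entry (envelope may be opened from here) → common induction → 30 min common TIVA → baseline FVEP → LD or HD maintenance → FVEP at 60 min. The allocation is first needed after the fourth step and is available from the first.

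**2. Can the anaesthesiologist's choices move the baseline?** The Background says "the P100 amplitude was significantly reduced at plasma concentrations of 3.0 μg/ml propofol compared to 1.5 μg/ml, even during TIVA", so the protocol itself treats propofol level as relevant to amplitude. That contrast is twofold (3.0/1.5 = 2). The permitted baseline range starts where it ends and spans a ratio of 4/3 = 1.33. The remifentanil range is fourfold (0.2/0.05 = 4). The BIS target of 40 to 50 is described through propofol adjustment in LD and desflurane titration, so it is not clearly tied to the TIVA phase. The route exists, but the documents give no effect size within these ranges.

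**3. Effect on a decline rate.** Let d = 1 − A/B, with A the 60-min amplitude and B the baseline. If B is shifted by a fraction s and A is unchanged, the observed decline is d′ = 1 − (1 − d)/(1 + s). The values d = 30% and s = ±10% are assumptions, not protocol figures:
- s = +0.10: 1 − 0.70/1.10 = 36.4%
- s = −0.10: 1 − 0.70/0.90 = 22.2%

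Now use the planning amplitudes (Sample size calculation: LD 3.43, HD 2.37 μV). No baseline amplitude is given, so assume 4.0 μV in both arms, with a range of 3.43 to 5.0:
- LD, no shift: (4.0 − 3.43)/4.0 = 14.2%
- LD, baseline 10% lower: (3.6 − 3.43)/3.6 = 4.7%, a change of 9.5 points. The change is 11.1 points from a baseline of 3.43 and 7.6 points from 5.0.
- HD, no shift: (4.0 − 2.37)/4.0 = 40.8%

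The primary contrast, 3.43 − 2.37 = 1.06 μV, contains no B and does not change.

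**4. Effect of losing randomised patients.** The plan's inflation reproduces: 63/(1 − 0.10) = 70. The margin is 0.20 × 2.37 = 0.474 μV, so the effective difference is 1.06 − 0.474 = 0.586 μV. A noncentral-t calculation at one-sided 0.025 with common SD 0.80 needs 31 per arm, 62 in total, against the stated 63. With SDs 0.78 and 0.80, power from 70 randomised is:

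| Loss | Power |
|---|---|
| 0% | 86.4% |
| 1.7% | 85.8% |
| 10% | 82.6% |
| 15% | 80.3% |
| 20% | 77.8% |

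At the earlier study's 1.7% dropout, 0.017 × 70 is about one patient. The planned 10% allows for seven. What is at issue is the completeness of the randomised set, not power.

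**The case against.** The case against is substantial, and much of it stands.

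- **A reader might infer that the envelope is opened before induction.** That is the natural reading, since room entry is the only time marker, but the text does not say it and the flow diagram is not shown. What can be said is that nothing prevents early opening.
- **A reader might infer that the baseline is unprotected.** It is not. The recorder is blinded, one neuroelectrophysiologist monitors every case, three measurements are averaged, and both arms share the same TIVA ranges and the same haemodynamic and temperature limits. This leaves only the anaesthesiologist's choice within the ranges, and nothing shows that it would differ by arm or in which direction.
- **A reader might infer that the primary result is at risk.** The primary endpoint does not use the baseline, and no baseline adjustment of it is stated.
- **A reader might infer that allocation concealment fails.** Consent precedes randomisation, the sequence is generated independently, and the envelopes are closed and opaque.
- **Baseline failures should be rare.** The Discussion reports 100% monitoring success in the group's previous study, and visual impairment is an exclusion. Failures would come before the treatments differ and be judged by a blinded recorder, so they are probably non-differential. The exclusion itself comes from the Statistical analysis section, which does not say whether a missing baseline with a valid 60-min value counts as having no available data.
- **Randomising only patients with a usable baseline has a price.** It adds an intraoperative eligibility condition and makes the FVEP success-rate endpoint conditional on earlier success.

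These points limit the concern but do not remove it. A blinded recorder cannot correct an anaesthetic state chosen by someone who knows the arm, and the price in the last point does not attach to simply opening the envelope later.

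**Conclusion.** The point holds in a limited form. The protocol lets an unblinded clinician learn the arm before a baseline that both arms share and that this clinician can influence within the permitted ranges. Three secondary endpoints could be biased as a result; the arithmetic of the primary endpoint is untouched. The bias is possible, not shown, and its size cannot be derived from the documents. The movement from 30% to about 36% or 22% rests on an assumed 10% arm-specific baseline shift, an assumed true decline and an unchanged 60-min value. Recording failures at baseline become avoidable post-randomisation losses, probably few and balanced, with power at or above 80% up to about 15% total loss. This is a cheap design improvement and not a flaw that undermines the main comparison.

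**What to change.** In Randomization and blinding, state that the envelope is opened only after the 30-min TIVA baseline FVEP recording has been completed and stored, and record the time of opening. This changes no drug, measurement or sample size (63/0.9 = 70 still applies). The cost is a short amendment, and set-up must be ready for either arm during the case.

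Declining to randomise patients without a usable baseline is a separate choice. If it is made, log and report those patients, submit the eligibility change as Ethics and dissemination requires, and either state that the FVEP success rate is conditional on a usable baseline or also report it over all monitored eyes. If it is not made, reconcile Remedy with Statistical analysis on whether patients with failed recordings stay in the analysis.

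Recruitment began in July 2022 with completion estimated for 1 June 2024, so an amendment may reach few patients. For those already enrolled, report by arm the propofol and remifentanil given during the baseline phase and the number of baseline recording failures, with envelope-opening times if they were noted. If the procedure changes mid-trial, identify which patients were randomised under each version.
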